### Additional note on preprocessing of neurobiological data (outcomes 4a and 4b}

#### Electroencephalography

The electrophysiological data set will be amplified using the BrainAmp™ acquisition system (Brain Products, Inc.) using a sampling rate of 1 kHz, a resolution of 0.1 μV, and bandpass analog filtering between 0.01 and 500 Hz. A principal component analysis will remove artifactual sources. Temporal periods ranging from −200 ms to 750 ms around the emission of each auditory stimulus will be extracted and normalized to baseline using the standard analysis methods recommended for the MatLab software, version 2017a with relevant toolboxes (EEGLab, ERPLab). Time-frequency analyses by Fourier transform will be conducted with a calculation of inter-trial coherence and average spectral powers over the duration of the per-stimuli time periods. Time domain analyses will be conducted with a calculation of event-related potentials amplitude during the auditory oddball tasks (N1, MMN, P300). The sLORETA source imaging technique (http://www.uzh.ch/keyinst/loreta.htm) will be used to examine the temporal activation of brain regions contributing to the observed event-related potential modulation patterns.

#### Magnetic resonance imaging

The acquired data (images, spectra, and raw data) will be transferred to a server for centralization (Shanoir, https://project.inira.fr/shanoir).

aMRI and rsfMRI: pre-processing including movements realignment, correction of geometrical distortions, “slice timing,” coregistration to the anatomical image, normalization to the reference MNI (Montreal Neurological Institute/International Consortium for Brain Mapping stereotactic space) standard space, spatial smoothing, and additional filters will be performed using the SPM software (Statistical Parametric Mapping https://www.fil.ion.ucl.ac.uk/spm). Then, the correlation rates of the preprocessed signals sensitive to BOLD fluctuations will be regressed both on the whole-brain for whole-brain analyses and at the level of cortical areas stimulated by tDCS (left prefrontal and temporal cortices) for region-of-interest analyses as functional connectivity indices (z-scores) using the SPM CONN toolbox.

MRS: pre-processing of spectroscopy data including ER-filtering of the spectra frequencies, phase dynamics correction (Gabor tool), and the Cadzow procedure for noise reduction (Cadzow procedure) will be conducted using the jMRUI124 software (http://www.jmrui.eu). Then, Glutamine and GABA levels (mM) localized in the cortical areas stimulated by tDCS (left prefrontal and temporal cortices) will be extracted and normalized to a reference metabolite using a recently developed tool specifically for GABA quantification (GABA MRS http://www.gabamrs.com).

PET-MRI: Dynamic PET will be corrected for possible subject motion [56]. Through examination of the PET time-activity curves of the radiotracer [^11^C]flumazenil, changes in extracellular GABA levels will be estimated by calculating the radiotracer binding. Parametric maps of non-displaceable binding potential (BP_ND_) [^11^C]flumazenil will be modeled with the SRTM model using the pons as a reference region (region devoid of GABA-A receptors). Regional BP_ND_ extraction will be performed for the left prefrontal and temporal cortices. Group voxel-to-voxel statistical analyses will be performed in the MNI space with the SPM toolbox.

### Interim analyses {21b}

The study will have no interim analysis.

### Methods for additional analyses (e.g., subgroup analyses) {20b}

Subgroup analyses will be performed regarding possible confounders such as the study site. In case of baseline differences between the 2 groups (active tDCS and sham tDCS), statistical analyses will be adjusted to take into account specific variables that may have influenced the results (e.g., antipsychotic dosage, illness duration, and age).

### Methods in analysis to handle protocol non-adherence and any statistical methods to handle missing data {20c}

Protocol non-adherence will be described as follows: characteristics at inclusion, arm (active tDCS or sham tDCS), withdrawal date and visit number, reason for withdrawing, and last outcomes carried forward. For the trial (*N*=60), the analyses will be conducted on the intention-to-treat set, including all randomized participants with at least one assessment conducted after the tDCS treatment (10 sessions). Per protocol analyses will be performed using the whole sample (*N*=60). The last observation carried forward will be used for missing data.

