### Criteria for discontinuing or modifying allocated interventions {11b}

Modification of the allocated intervention for a given participant (active tDCS or sham tDCS) based upon any reasons will not be allowed. In case of tDCS treatment discontinuation, the participant will be withdrawn from the study.

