### Sample size {14}

Based on previous tDCS studies in patients with schizophrenia (rev. in [17], we assume that a third (33%) of participants in the active tDCS group and 5% of participants in the sham tDCS group will be responders (improvement greater than or equal to *Z*=0.5 from baseline on the MCCB total score). Based on this estimated difference, we calculated that 60 patients are required to demonstrate a difference between the two groups with a power of 80% (*p* = 0.05).

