## Statistical methods

### Statistical analysis plan

In general, the normality of the data distributions will be investigated with Shapiro-Wilk tests. Between-group comparisons will be performed with Mann-Whitney *z*-tests and two-sample *t*-tests for non-normal and normal continuous outcomes, respectively. Categorical data will be compared with chi-square tests. Both intention-to-treat and per-protocol analyses will be conducted. In case of significant interactions, post hoc analyses will be conducted using appropriate contrasts. Analyses will be adjusted or stratified by the study site as part of a sensitivity analysis. The significance threshold will be set at *P*-value < 0.05 and appropriate effect sizes of significant results will be calculated.

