### Statistical methods for primary and secondary outcomes {20a}

#### Main outcome

The percentage of “responders” showing an improvement in global cognitive improvement (increase ≥ 0.5 of the global MCCB *Z*-score at 1-month follow-up) will be compared between the active tDCS group (*N*=30) and the sham tDCS group (*N*=30) using a chi-square test. In addition, a binomial test will be used to test the superiority of the proportion of responders to active tDCS vs. sham tDCS.

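### The intention-to-treat set excludes anyone who stops tDCS early, while the per-protocol set is all 60 participants: the two definitions are in effect swapped

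*Protocol article*

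**What the plan says.** The Statistical analysis plan section promises two analyses: "Both intention-to-treat and per-protocol analyses will be conducted". Section {20c} defines the sets. It states that "the analyses will be conducted on the intention-to-treat set", described as "including all randomized participants with at least one assessment conducted after the tDCS treatment (10 sessions"). The next sentence reads "Per protocol analyses will be performed using the whole sample (*N*=60"), and the section closes with "The last observation carried forward will be used for missing data".

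Section {11b} adds: "In case of tDCS treatment discontinuation, the participant will be withdrawn from the study".

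The Main outcome section says that the responder percentage "will be compared between the active tDCS group (*N*=30) and the sham tDCS group (*N*=30) using a chi-square test", so it assumes that all 30 participants per arm are analysed. The sample size section {14} makes the same assumption and includes no allowance for loss.

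**The concern.** An intention-to-treat set should not depend on what happens after randomisation. This one requires a post-treatment assessment, and {11b} removes from the study the people least likely to have one. Early stopping can result from poor tolerance or clinical worsening. Section {17b} on unblinding itself foresees worsening that ends the protocol and serious adverse effects. If such events differ by arm, the primary comparison is no longer between the groups formed by randomisation.

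The per-protocol set is meant to show what happens among participants who adhered. Defined as everyone, it cannot do that, and it is at least as large as the intention-to-treat set. An analyst who follows the Main outcome section uses 30 versus 30. One who follows {20c} uses fewer as soon as anyone stops early.

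**Working it through.** **1. Who is in which set, reading {11b} and {20c} together**

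| Participant | Intention-to-treat set as written | Per-protocol set as written |
|---|---|---|
| Completes 10 sessions, attends 1 month | In | In |
| Completes 10 sessions, has end-of-treatment ratings, misses 1 month | In, with LOCF | In |
| Stops tDCS early, withdrawn from the study | Out: no assessment after treatment | In: whole sample |

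LOCF does not bring the third participant back, because set membership is decided before missing values are filled. The second and third rows also treat similar losses differently. If no MCCB was taken after baseline, the second participant carries the baseline score forward, shows zero change and counts as a non-responder. The third leaves the denominator.

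**2. The plan's own sample size**

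Inputs from {14}: "we assume that a third (33%) of participants in the active tDCS group and 5% of participants in the sham tDCS group will be responders"; 80% power; p = 0.05, taken as two-sided. The pooled rate is (0.33 + 0.05)/2 = 0.19.

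n per arm = [1.96·√(2·0.19·0.81) + 0.842·√(0.33·0.67 + 0.05·0.95)]² / 0.28² = (1.087 + 0.436)² / 0.0784 ≈ 29.6, rounded up to 30, or 60 in total.

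The stated 60 is reproduced, with power of 80.5% at 30 per arm. It is not in dispute, but it leaves almost no slack.

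**3. Effect on the active response rate (illustration)**

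Assume 10 responders among 30 active participants and early stoppers who are all non-responders:

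- All randomised: 10/30 = 33.3%
- 3 early stoppers removed: 10/27 = 37.0% (+3.7 points)
- 5 early stoppers removed: 10/25 = 40.0% (+6.7 points)

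**4. Unequal stopping (illustration)**

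Assume 6 active and 1 sham early stoppers, and 7 versus 2 responders. The test is the uncorrected chi-square, N(ad − bc)² / (product of the four margins).

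- Set as written, 7/24 versus 2/29 (29.2% versus 6.9%): 53·(7·27 − 17·2)² / (24·29·9·44) = 4.62, p = 0.032
- All randomised, 7/30 versus 2/30 (23.3% versus 6.7%): 60·(7·28 − 23·2)² / (30·30·9·51) = 3.27, p = 0.071

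**5. Equal stopping in both arms**

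No dropout rate is given, so 0 to 25% is assumed. In the set as written, the rates stay at 33% and 5% among those kept. In the all-randomised set, both rates are multiplied by (1 − stopping rate).

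| Early stopping | Kept per arm, as written | Power, as written | Rates, all 60 | Power, all 60 |
|---|---|---|---|---|
| 0% | 30 | 80.5% | 33.0% vs 5.0% | 80.5% |
| 10% | 27 | 76.1% | 29.7% vs 4.5% | 74.9% |
| 20% | 24 | 70.8% | 26.4% vs 4.0% | 68.5% |
| 25% | 22.5 | 67.9% | 24.7% vs 3.8% | 65.0% |

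**The case against.** The strongest reply is that {20c} alone does not exclude early stoppers. The bracketed 10 sessions may simply describe the course, and the exclusion appears only when {11b} is added and withdrawal is taken to mean no further assessment. The opening sentence of {20c} also lists last outcomes carried forward among the items reported for non-adherent participants, which suggests that withdrawn people were expected to have outcomes. It is true that two sections must be combined. But {11b} says withdrawn from the study, not merely from treatment, and a descriptive list does not override an explicit membership rule.

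The phrase whole sample might mean only the four-centre sample, as opposed to the single-centre PET-MRI group. Even so, the sentence sets no adherence condition and gives N as 60, so no per-protocol set is defined.

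Three limits stand. Completers here means treatment completers; someone who finishes the one-week course and misses the 1-month visit stays in through LOCF. The illustrations in steps 3 and 4 rest on assumed counts, and the trial's own hypothesis is that tolerance will not differ between arms. With equal stopping, the choice of set moves power by only 1.2 to 2.9 points over the 10 to 25% range.

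The point cannot be left to a later analysis plan. The article fixes both sets explicitly, and {31c} presents it as the full protocol.

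**Conclusion.** The concern holds. The intention-to-treat set is conditioned on completing treatment, and the per-protocol set is everyone randomised. The primary estimate is therefore one among treatment completers, and the planned per-protocol analysis says nothing about adherence.

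The size and direction of any bias cannot be known from the document. If nobody stops early, the two sets coincide. Under the assumed counts, the active rate rises by about 4 to 7 points without any added benefit, and unequal stopping can place the two sets on opposite sides of 0.05. Because this affects the primary superiority comparison, and outcomes not collected cannot be recovered later, it must be corrected before unblinding and as early in follow-up as possible.

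**What to change.** - **Primary set, {20c}:** all 60 randomised participants, analysed in their allocated arm. A missing 1-month MCCB counts as non-response, replacing LOCF for this endpoint, with multiple imputation as a sensitivity analysis.
- **Per-protocol set, {20c}:** participants who received all 10 allocated sessions, have a 1-month MCCB and have no major deviation.
- **Outcome collection, {11b}:** separate stopping stimulation from leaving the study, so that scheduled outcome visits continue in participants who agree. This changes data collection only, not when stimulation is stopped.
- **Consistency:** bring {11b}, {20c}, the Statistical analysis plan section and the Main outcome section into line on the denominators.

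The cost is a change of wording and a few visits that are already in the schedule. The active response rate may look slightly less favourable. Under equal early stopping of 10 to 25%, the all-randomised rule gives 1.2 to 2.9 points less power than the set as written. The larger fall from 80.5% comes from the stopping itself and occurs under either definition.

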### Plans to give access to the full protocol, participant level-data and statistical code (31c}

The present document describes the full protocol. Statistical codes and anonymized participant-level data will be available from the principal investigator upon reasonable request.

### Composition of the data monitoring committee, its role and reporting structure {21a}

Data monitoring reports will be ensured by an independent committee mandated by the principal study site (CHU Grenoble Alpes). The members of this committee have no relationship with the investigators and no competing interest related to the study. The initial committee meeting will take place prior to the start of the trial. The committee will meet at least once a year to assess the trial's progress and safety. Prior to each meeting, no data analysis will be performed. If necessary, the trial expansion will be discussed at the final committee meeting. Throughout the trial period, at least annual onsite monitoring visits will be planned to verify the accuracy and quality of the data.

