## Assignment of interventions: blinding

### Who will be blinded {17a}

Blinding will be maintained at 3 levels: participants, research staff members including investigators, and data analysts. If different from the investigator, care providers will be also blinded to the intervention. Blinding for the tDCS condition will be achieved for the research staff members who will administer the tDCS by the use of a randomization code (see details in §16c) and for the participants by ensuring identical appearance and sensation for both active and sham conditions (see details in §6b). The duration of the intervention will be 20 min in both active and sham sessions. Outcome assessments, imaging, and biological data will be collected and analyzed by research staff members blind to group assignment and different from the staff member who will administer the tDCS.

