### Procedure for unblinding if needed {17b}

Unblinding will be permissible under the following circumstances during the trial period: appearance of non-inclusion criteria, withdraw of consent to participate in the study, worsening of the clinical condition observed by the investigator justifying the discontinuation of the protocol, and serious adverse effects. Participant’s allocated intervention will be revealed to the subject by the investigator who enrolled the participant.

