##### Secondary outcome 3: tolerance

Outcome 3: tDCS tolerance questionnaire scores measured after tDCS will be compared between the active tDCS and sham tDCS groups using mean comparison tests.

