### Adverse event reporting and harms {22}

Safety assessment will be conducted according to the requirements of the MDR 2017/745 and MDCG 2020-10/1 statements (European commission) and article of the R1123-46 (French Public Health Code). The investigator will document in the CRF any adverse event observed of reported by the participant. The causal link with the use of the medical device (tDCS) will be assessed. Any adverse event will be monitored until it is completely resolved.

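### The monitoring committee is to assess safety at least yearly, yet an unqualified bar on data analysis before each meeting, read literally, rules out a by-arm summary of harms

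*Protocol article*

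**What the plan says.** Two adjacent sentences in the committee section {21a} are at issue. The first sets the task: "The committee will meet at least once a year to assess the trial's progress and safety". The second follows directly: "Prior to each meeting, no data analysis will be performed". It names no type of data and carries no exception.

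Other sections bear on the point:

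- Interim analyses {21b}: "The study will have no interim analysis".
- Who will be blinded {17a}: "Blinding will be maintained at 3 levels: participants, research staff members including investigators, and data analysts".
- Adverse event reporting and harms {22}: "The investigator will document in the CRF any adverse event observed of reported by the participant". A causality assessment against the device is added, under the European device rules and French law.
- Procedure for unblinding if needed {17b}: unblinding is allowed for, among other reasons, serious adverse effects and clinical worsening that leads to discontinuation. It then says: "Participant’s allocated intervention will be revealed to the subject by the investigator who enrolled the participant".
- Statistical methods, secondary outcome 3: "tDCS tolerance questionnaire scores measured after tDCS will be compared between the active tDCS and sham tDCS groups using mean comparison tests".

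**The concern.** A committee that judges the safety of a sham-controlled trial needs to know whether events gather in one arm. A causality judgement on a single case cannot show this, and neither can a pooled count. The text sets a safety task and, in the next line, withholds the summary that would most directly serve it.

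What is at stake is how early an imbalance in harms could be recognised. The adverse effects questionnaire itself covers headaches, neck pain, mood alterations and seizures, so the authors regard these as possible. If the sentence is followed as written, a pattern across participants has no stated route to the committee before the end of the trial.

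The end-of-trial comparison may not make up for this. The planned tolerance outcome is scored after the last session, and a participant who discontinues tDCS is withdrawn from the study {11b}. The intention-to-treat set requires at least one assessment after the 10 sessions {20c}. Someone who stops early because of an adverse event may therefore be absent from the tolerance comparison.

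**Working it through.** The plan gives no figure on this point, so the check is a comparison of sections.

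1. **Task.** Committee section {21a}: assess progress and safety, at least yearly.
2. **Restriction.** Same section, next sentence: no data analysis before each meeting. It is not limited to efficacy.
3. **Is the restriction needed for the type I error?** Section {21b} already states that there is no interim analysis. If the sentence in {21a} means only that efficacy is not examined, it repeats {21b}. If it means all data, it reaches safety tables, where no primary-outcome test is at issue. On neither reading does it add protection. The planned 60 participants (33% versus 5% responders, 80% power) and the 0.05 threshold do not depend on it.
4. **Does another section supply a by-arm view of harms to the committee?**
   - {22} provides for recording and causality assessment of single events. It names no summary and no report to the committee.
   - {17b} permits individual unblinding. The stated recipient of the allocation is the participant, and the committee is not named.
   - Secondary outcome 3 compares tolerance scores between arms, but does not tie this to committee meetings.
   - {17a} blinds participants, research staff including investigators, and data analysts. It mentions neither the committee nor any sponsor safety function.
   - None of these gives the committee a between-arm summary.
5. **How much could a by-arm table show?** The documents state no event rate, so only precision can be illustrated. With no events among n active participants, the one-sided 95% upper bound on the risk is 1 − 0.05^(1/n).
   - Assume even accrual over about three years (recruitment from winter 2022 to 2025): 60/3 = 20 a year, or 10 per arm. Then n = 10 gives 1 − 0.05^(1/10) = 0.259.
   - At full enrolment, n = 30 gives 1 − 0.05^(1/30) = 0.095.
   - A single yearly table is therefore imprecise, and totals should accumulate over meetings.

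**The case against.** The strongest reply is that barring analysis is not barring data. The committee section opens by speaking of data monitoring reports, and a committee can review event reports and listings without any statistical analysis. Read beside {21b}, the sentence may only restate that no interim efficacy analysis is prepared. Details such as who holds the code normally sit in a charter, which a journal article need not reproduce.

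Much of this stands. A reader might infer three stronger things, and the documents support none of them:

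- **That the committee cannot assess safety at all.** Individual adverse event reports and listings are not excluded by the wording.
- **That harms would stay blinded until the end.** Section {17b} permits unblinding for serious adverse effects and for clinical worsening that leads to discontinuation. It permits rather than requires this, but such cases need not remain blinded.
- **That nobody could compare the arms during the trial.** Section {17a} does not blind the committee or the sponsor's safety function, and the sponsor generates the randomization list {16a}.

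The reply does not remove the conflict between the two sentences. The efficacy-only reading is plausible, but the text does not say it. A charter that gave the committee a by-arm harm summary would depart from the sentence as written. The point therefore rests on a stated rule, not on a missing detail. The imprecision of early by-arm counts is real, but it is a reason to accumulate them, not to withhold them.

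**Conclusion.** The point holds in a limited form. The committee section sets a safety task and then, without qualification, excludes data analysis before each meeting. Read literally, this rules out a compiled by-arm summary of harms, and no other section provides one. Individual reports and case-by-case unblinding remain available, so oversight is weakened, not absent.

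The conclusion assumes that the sentence is applied as worded and that a table of events by arm counts as data analysis. If the authors meant efficacy only, the defect is one of wording, and the same correction settles it. The size cannot be quantified from the documents because they give no event rate. There is no effect on the primary endpoint, the sample size or the type I error. The change should be made because it concerns safety oversight and costs little.

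**What to change.** Reconcile the two sentences in the committee section {21a}. Possible wording:

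> No efficacy analysis will be performed before any meeting. Before each meeting the committee will receive a cumulative tabulation, by coded arm, of adverse events, serious adverse events and tDCS discontinuations with reasons, prepared from the eCRF by a person outside the blinded trial team.

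Section {21b} can stay as it is. The committee's powers to recommend action, and the detailed handling of closed reports, can be left to its charter.

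The cost is one amended paragraph and a short table about once a year, from data already collected. The small downside is that the coded allocation must be handled by someone outside the blinded team. No type I error is spent, because efficacy is not examined.
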